## Abstract

**Background:**

In rural Ethiopia, 72% of women are exposed to lifetime intimate partner violence (IPV); IPV is most prevalent during pregnancy. As well as adversely affecting women’s physical and mental health, IPV also increases the risk of child morbidity and mortality associated with maternal depression, thus making antenatal care an important opportunity for intervention. Adapting generic, task-shared, brief psychological interventions for perinatal depression and anxiety to address the needs and experiences of women affected by IPV may improve acceptability to women and feasibility for health workers. This randomised controlled feasibility trial will compare brief problem solving therapy (PST) specifically adapted for pregnant women experiencing IPV (PST-IPV) with standard PST and enhanced usual care to determine the feasibility of a future fully powered randomised controlled trial.

**Methods:**

Seventy-five pregnant women scoring five or more on the Patient Health Questionnaire, endorsing a tenth question about functional impact and reporting past-year IPV, will be recruited from antenatal care clinics in predominantly rural districts in Ethiopia. Consenting participants will be randomised to either four sessions of PST-IPV, four sessions of standard PST or information about sources of support (enhanced usual care) in a three-arm design. The interventions will be delivered by trained, supervised antenatal care staff using a task-sharing model. Assessments will be made at baseline and after 9 weeks by masked outcome assessors and will include measures of depression symptoms (primary outcome), post-traumatic stress, anxiety symptoms, functional impact, past-month IPV and hypothesised mediators (secondary outcomes). A mixed-method process evaluation will determine the feasibility of a future randomised controlled trial, assess the feasibility, acceptability, fidelity and quality of implementation of PST-IPV, generate testable hypotheses about causal mechanisms, and identify potential contextual factors influencing outcomes.

**Discussion:**

Despite mental health being a critical concern for women experiencing IPV, there is limited evidence for brief, task-shared psychological interventions adapted for their needs in low- and middle-income countries. Contextually tailored interventions for pregnant women experiencing IPV in low- and middle-income countries require development and process evaluation. This randomised controlled feasibility trial will yield results on the feasibility of conducting a fully powered trial, relevant to researchers, primary and antenatal care clinicians in resource-limited settings.

**Trial registration:**

Pan-African clinical trials registry: PACTR202002513482084. Prospectively registered on 13 December 2019.

## Introduction

### Background and rationale

Intimate partner violence (IPV) refers to behaviour by a partner or ex-partner that causes (or has the potential to cause) physical, sexual or psychological harm. IPV includes physical aggression, sexual coercion, psychological abuse and controlling activity [1]. It is highly prevalent worldwide [2] and an important social determinant of physical and mental health [3, 4]. In response, the World Health Organization (WHO) [5], the United Nations [6] and the World Psychiatric Association [7–9] have prioritised interventions to prevent and address IPV and its health impacts.

The relationship between IPV and mental health is bidirectional, such that IPV increases a woman’s risk of mental disorders, which in turn increases a woman’s vulnerability to (further) IPV. For example, IPV is associated with subsequent depressive symptoms, suicide attempts [10] and alcohol use disorders [11], which increase women’s risk for IPV (re)victimisation. Exposure to IPV is rarely assessed in randomised controlled trials (RCTs) of psychological interventions [12], but some studies have found reduced IPV alongside improved mental health [13] and birth outcomes [14].

There is limited evidence on mental health interventions tailored to the needs of pregnant women experiencing IPV [15], especially in low- and middle-income countries (LMICs). In a rapid review of evidence, 33 studies were identified that reported mental health interventions for women affected by IPV [16]. In most of these studies, the interventions were group-delivered cognitive behavioural therapy (CBT)-informed interventions, mind–body interventions (such as mindfulness-based stress reduction, yogic techniques and biofeedback) or individually delivered, trauma-focused psychotherapeutic interventions. Although all the identified studies came from high-income countries, protocols from Tanzania [17] and South Africa [18] indicated growing research interest in the African region. For example, one RCT in Nairobi, Kenya, has shown that five sessions of the multicomponent behavioural treatment Problem Management Plus (PM+) delivered to women with a history of any gender-based violence are associated with improved psychological distress and post-traumatic stress symptoms at 3-month follow-up compared with enhanced usual care [19].

A recent systematic review confirmed the paucity of intervention research addressing the mental health of both survivors and perpetrators of IPV in LMICs [20]; no studies replicated evaluations of previously studied interventions and none were conducted in low-income countries. The authors recommended strengthening the theoretical underpinnings of mental health interventions for people experiencing or perpetrating IPV, testing their impacts on hypothesised mediators and improving IPV detection using continuous outcome measures and fully powered samples. Treating depression and post-traumatic stress disorder (PTSD) has the potential to reduce self-blame, low self-esteem, hopelessness and emotional numbing, and improve communication, stress coping and anger management skills among both survivors and perpetrators [20].

We recently investigated whether IPV exposure moderates the efficacy of generic psychological interventions in LMICs. Our meta-analysis of 15 studies that provided data showed that women reporting IPV demonstrated greater improvements in anxiety symptoms than women not reporting IPV following generic psychological interventions (difference in standardised mean differences, 0.31; 95% confidence interval 0.04–0.57; *I*^2^ 49.3%) and consistent but non-significant differences in PTSD, depression and psychological distress symptom improvements [21]. Our systematic review only identified two RCTs of psychological interventions for depression or anxiety in LMICs which were tailored for women experiencing IPV. In Pakistan, ten sessions of IPV-adapted group CBT were associated with improved depression and anxiety compared with CBT-based self-help groups [22]. In Iran, 10–12 sessions of IPV-tailored narrative exposure therapy were associated with improved PTSD and depression at 3- and 6-month follow-up compared with treatment as usual (life skills training and supportive counselling) [23]. These studies support the potential benefits of adapting psychological interventions for depression, anxiety or PTSD to meet the needs and experiences of women affected by IPV.

Although PM+ has been shown to be effective for women experiencing gender-based violence in Nairobi [19], delivering five 90-min sessions may not be feasible in primary care settings in low-income countries. Problem solving therapy (PST) is a brief psychological intervention that aims to improve coping with life problems by teaching problem solving skills. A meta-analysis of PST for depression found a standardised mean effect size of 0.34, but high heterogeneity among included studies indicated the need for research to determine the settings and patient groups for whom PST is most effective [24]. A meta-analysis of PST for any mental or physical health problem found that it was significantly more effective than no treatment, treatment as usual, and ‘attention placebo’ arms (controlling for non-specific effects of contact), moderated by the use of problem orientation training and homework assignments [25].

Several studies from LMICs suggest that PST can be effective for treating depression, anxiety and psychological distress. A 5-week pilot study of adapted PST in English, Xhosa and Afrikaans in South African township residents found that it was acceptable, feasible and associated with significant reductions in psychological distress [26]. An RCT of South African emergency department attendees found that substance use was significantly reduced at 3-month follow-up in participants who received five sessions of blended PST and motivational interviewing, compared to motivational interviewing alone or psychoeducation control [27]. In Zimbabwe, the ‘Friendship Bench’ intervention comprised six sessions of individual PST delivered by lay health workers, and an optional six-session peer support group [28]. In this 86% female sample, depression and psychological distress were significantly reduced following PST in comparison to enhanced usual care.

The importance of designing RCTs to evaluate mediators of treatment and mechanisms of change is widely supported [29]. However, despite evidence of efficacy, studies of how PST works are limited and contradictory. Hypothesised mechanisms have included improving mastery, self-control and the accuracy of perceived problem severity [30], problem solving skills [31], ‘life integration’ [32] and locus of control (the extent to which the individual attributes their experiences to internal or external factors) [33]. An RCT comparing online CBT, PST and waiting list control for depression found that the effects of both interventions were mediated by reduced dysfunctional attitudes, worry, negativity towards problems and increased mastery, with no difference in effect sizes between CBT and PST [34]. The authors postulated that both interventions increase expectations of self-efficacy, leading to greater commencement and continuation of coping behaviours [35]. Both mechanisms for improved mood might also influence the ability of women to respond to IPV.

Process evaluations of complex intervention feasibility studies are increasingly recognised as being vital to optimise the safety, efficiency and validity of subsequent RCTs [5, 36]. Updated guidance [37] and growing consensus [38] support the need for studies to determine the feasibility of research methods used to study complex interventions before conducting definitive RCTs. Sociocultural, health system and economic factors affect the adaptation, translation, mechanisms, success and scale-up of interventions, so a mixed-method process evaluation [39] is crucial and helps to inform understanding of the context for future implementation [40].

In rural Ethiopia, 72% of women are exposed to lifetime IPV [41] and this is associated with emotional distress [42] and depression [43]. IPV in Ethiopia is most prevalent during pregnancy [44] and increases the risk of child morbidity and mortality associated with maternal depression [45]. Antenatal depression in Ethiopia is associated with increased emergency presentations in pregnancy [46], perinatal complications [47], prolonged labour [48] and use of emergency delivery care [49]. As pregnancy is the most common time for Ethiopian women to access health care [50], antenatal care offers an important opportunity to provide an intervention that addresses both IPV and depression.

The range of cultural, geographical, economic, linguistic, religious, socio-political, health system and other differences between rural Ethiopia and the largely middle-income settings of most RCTs published to date supports the need for research evaluating PST adapted for women experiencing IPV (PST-IPV) in this context.

### Objectives

In this randomised feasibility trial and process evaluation of perinatal PST-IPV in rural Ethiopia, we aim to determine the feasibility and acceptability of the intervention and study design to inform a future fully powered RCT. Specific objectives are to:
Determine whether the PST-IPV intervention and processes of recruitment, randomisation, follow-up and evaluation are feasible and acceptable to pregnant women and health workers in rural Ethiopia. This includes estimating parameters to inform the design of a future RCT.Refine the PST-IPV intervention and study design in response to a mixed-method process evaluation, which assesses the feasibility, acceptability, fidelity and quality of the intervention, explores causal mechanisms, and identifies contextual factors that may influence outcomes [37].

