### Participant sample size

As a feasibility trial, this study is not powered to detect intervention efficacy, but rather to estimate feasibility parameters to inform a future RCT, and test intervention and research protocols. With a total sample size of 75 (25 participants randomised to PST-IPV, 25 to PST and 25 to enhanced usual care), a drop-out rate of 30% can be estimated to within a 95% confidence interval of ±3%. To estimate the standard deviation of the primary feasibility outcome measure to inform a future RCT sample size calculation, recommended feasibility trial sample sizes range between a total of 24 and 50 across two arms [56, 57].

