#### Primary participant outcome

At baseline and the independent, masked, 9-week follow-up interview, depression symptoms will be measured using the Amharic-translated PHQ-9 [59], a nine-item questionnaire asking about the presence of depressive symptoms in the preceding 2 weeks. Each item is rated according to persistence of the symptom (0 = not at all, 1 = several days, 2 = more than half of the days, 3 = nearly every day). PHQ-9 scores pre- and post-participation will be compared to calculate the mean difference in depression symptom reduction in PST-IPV, standard PST and enhanced usual care arms. Proportions of participants showing a treatment response, defined as a 50% reduction in PHQ-9 score, will also be calculated, although this feasibility trial will not be powered to detect treatment efficacy.

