### Measurement: process evaluation

#### Assessing parameters and feasibility for a future trial

The mixed-method process evaluation will assess variables associated with intervention implementation processes. Recommended intervention process outcomes (for implementation) include acceptability, adoption, appropriateness, feasibility, fidelity, implementation cost, penetration and sustainability [78]. In this feasibility trial, we will focus on evaluating:
Acceptability of PST-IPV and of the study design to women and health workers in terms of uptake, completion and drop-out ratesAdoption by health workersAppropriateness from women and health workers’ perspectivesFeasibility in terms of practical organisationFidelity of deliveryCostSafety

The following administrative data will be collected, which will inform the feasibility outcome measures shown in brackets:
Screening rates and reasons for refusal (acceptability)Recruitment rates (acceptability, feasibility)Numbers of eligible women at each clinical site (appropriateness)Proportions of eligible women agreeing to participate (acceptability)Willingness to be randomised and comprehension by participants of randomisation (acceptability of allocation)Session duration (appropriateness, feasibility, fidelity)Take-home activity completion (acceptability, fidelity, appropriateness)Drop-out rates (acceptability, feasibility)Follow-up rates (feasibility of retention)

Research staff will document key site features to enable comparison of process data, and keep field journals noting:
Staff willingness to participate at each site and retention in the study (acceptability, adoption, appropriateness, feasibility)Optimal recruitment procedures (feasibility)Acceptance of randomisation at each site (acceptability, appropriateness, feasibility)

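### Objective 1 is to establish feasibility, but the only defined primary outcome is the PHQ-9, and no feasibility rate is ranked primary or given a pre-specified progression criterion

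*Protocol article*

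**What the plan says.** Under Objectives, the first aim is to "Determine whether the PST-IPV intervention and processes of recruitment, randomisation, follow-up and evaluation are feasible and acceptable to pregnant women and health workers". The same item adds that this covers estimating parameters for the design of a later RCT. Objective 2 is to refine the intervention and the design.

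The primary label goes elsewhere. The Methods part of the Abstract says the assessments "will include measures of depression symptoms (primary outcome"). The section Primary participant outcome makes this the PHQ-9: "PHQ-9 scores pre- and post-participation will be compared to calculate the mean difference in depression symptom reduction" in the three arms, together with the proportion achieving a 50% reduction, "although this feasibility trial will not be powered to detect treatment efficacy".

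Participant sample size says "this study is not powered to detect intervention efficacy, but rather to estimate feasibility parameters to inform a future RCT". It then refers once to a primary feasibility outcome measure whose standard deviation is to be estimated, and does not say what that measure is. It also states that a 30% drop-out rate can be estimated to within ±3% with 75 women.

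The section Assessing parameters and feasibility for a future trial names seven process domains and a list of administrative data, each item tied to a domain, for example "Follow-up rates (feasibility of retention"). No item is ranked and none has a target or cut-off. Statistical analysis says the quantitative process data will settle improvements to the future RCT. Strengths and challenges expects those improvements to be made before a definitive trial.

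**The concern.** A feasibility trial should be able to say, by a rule fixed in advance, whether its main question was answered favourably. Here the word primary is attached to a clinical score that does not measure feasibility of recruitment, randomisation or follow-up. The measures that do bear on objective 1 carry no rank and no criterion. The article describes how process data will improve the next trial, but not what finding would argue against running it. What is at stake is the central conclusion: as the article stands, whether the trial proved feasible would be judged once the data are known, and a reader of the results could not check that judgement against a prior standard.

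**Working it through.** **1. Question against label.** Setting the sections side by side:

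- Objectives: the question is whether the intervention and trial processes are feasible and acceptable.
- Abstract (Methods) and Primary participant outcome: the primary outcome is depression symptoms on the PHQ-9.
- Participant sample size: a primary feasibility outcome measure is mentioned and not defined. Because it has a standard deviation, it reads most naturally as the PHQ-9.
- Assessing parameters and feasibility for a future trial: the rates that answer the question, with no rank and no threshold.
- The 30% drop-out in Participant sample size is a planning value for a precision statement. Nothing says that loss above 30% would count as infeasible.

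**2. The plan's own precision figure.** Inputs from Participant sample size: p = 0.30, n = 75, 95% confidence.

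- Half-width = 1.96 × √(0.30 × 0.70 / 75) = 1.96 × 0.0529 = 0.104, or ±10.4 points.
- Wilson interval for 22/75: 20.2% to 40.4%. Clopper-Pearson: 19.4% to 41.0%.
- The stated ±3 is not reproduced. It would need n = 1.96² × 0.21 / 0.03², which rounds up to 897.

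The denominators of other feasibility rates differ. At the same proportion (30% or 70%), the 50 women in the two therapy arms give 1.96 × √(0.21/50) = ±12.7 points, and a single arm of 25 gives ±18.0. For consent, the denominator is the number of eligible women approached, which the article does not give.

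These intervals describe sampling error. They show how precisely a rate can be known when bands are set. They do not measure the effect of reaching a verdict after the fact, and fixing bands would not narrow them.

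**3. Power on the PHQ-9.** This checks the article's own disclaimer. Using the standardised effect of 0.34 that Background and rationale cites for PST in depression (context there, not a design input), two arms of 25 and a two-sided 5% level:

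- Power ≈ Φ(0.34 × √(25/2) − 1.96) = Φ(−0.76) ≈ 22%.
- With 30% loss, 17.5 per arm: Φ(0.34 × √(17.5/2) − 1.96) = Φ(−0.95) ≈ 17%.

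This agrees with the statement that the trial is not powered for efficacy.

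**4. Could 75 women support a rule that a result might fail?** The article gives no threshold, so the cut-offs below are assumptions for illustration. P(proceed) is the binomial upper tail with n = 75.

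| Illustrative rule | True 60% | True 70% | True 80% | True 90% |
|---|---|---|---|---|
| At least 53 of 75 followed up (about 70%) | 0.04 | 0.51 | 0.98 | 1.00 |
| At least 60 of 75 followed up (80%) | 0.00 | 0.04 | 0.57 | 1.00 |

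Either rule separates true rates 20 points apart well. Neither discriminates when the true rate lies at the cut-off. The planned size can therefore carry a progression rule, with an amend band to absorb the uncertainty near the line.

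**The case against.** The strongest reply is that this is a study for estimating and refining. Objective 1 expressly includes estimating parameters, objective 2 is refinement, and Statistical analysis plans standard deviations and drop-out rates for a future sample size. On that view the PHQ-9 has a legitimate role, because its standard deviation is needed. The section heading also says primary participant outcome and stands apart from the process evaluation, and progression bands are only one way to run such a study. This stands in part: it is a reason to relabel the PHQ-9 and keep it. It does not remove the mismatch, since the Abstract uses the label without qualification, the sample size section leaves its own term undefined, and objective 1 still asks whether the processes are feasible.

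A second reply is that the full protocol, the supplementary files or an analysis plan may hold progression criteria. That cannot be excluded. The article points to none, however, and an analysis plan would not by itself correct which outcome the published protocol calls primary.

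A reader might go further and infer that no result whatever could show infeasibility. The article does not support that. It collects recruitment, willingness to be randomised, drop-out and follow-up, tied to named domains, and adds interviews on acceptability and burden. Very poor rates or adverse interview findings could still lead to a negative judgement. Only a result specified in advance is absent. Nor is the PHQ-9 comparison presented as an efficacy test: the article repeatedly says the trial is not powered for one.

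**Conclusion.** The point holds in this form. The only defined primary outcome does not answer objective 1, and the rates that do answer it have neither rank nor a pre-specified criterion, so no result fixed in advance could show infeasibility. The size of the harm from a verdict reached afterwards cannot be computed from the article. What can be computed is that a rate near 30% or 70% among 75 women is known to about ±10 points, roughly 3.5 times the stated ±3 (10.4 / 3), so anyone setting bands from the stated figure would make them too narrow. The conclusion assumes that no progression criteria exist in documents not shown. Participant safety is not affected. The change should be made, and Trial status says recruitment had not begun.

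**What to change.** Before recruitment, in the protocol and the registry entry:

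- Name three primary feasibility outcomes: the percentage of eligible women consenting to randomisation, the percentage of women in the two therapy arms attending all four sessions, and the percentage of randomised women with a PHQ-9 at 9 weeks.
- Have the team agree go, amend and stop bands for each, and report each rate with its 95% confidence interval. A 9-week band such as go at 70% or more and stop below 60% would be illustrative only, because the 30% drop-out in the article is a planning value and not an acceptability limit.
- Replace ±3% in Participant sample size with about ±10 percentage points, and set the bands with that figure in view. Allow for the smaller denominator of 50 for session attendance.
- In the Abstract, Participant sample size and Primary participant outcome, call the PHQ-9 the candidate primary outcome of the future RCT, and keep the estimate of its standard deviation.

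The cost is wording, through the amendment route already described in Trial status. The outcomes use data the trial already plans to collect, and the sample size does not change. The downside is that the team is bound to bands it must agree now.
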